#### Knowledge gaps

The prevalence of severe obesity has increased dramatically in Canada and bariatric surgery is currently the only effective treatment option offered to medical refractory patients. Identifying cost-effective strategies to treat severe obesity must be a priority for governments and healthcare systems as healthcare expenditures of severely obese adults are double that of normal weight individuals [60]. Since 2003, there has been an exponential increase in the number of LSG’s performed as a treatment for severe obesity. There is evidence to support the efficacy of LSG in terms of weight loss and comorbid improvement/resolution, however data on other outcomes are limited (e.g., weight loss sustainability or recidivism, comorbid regression, nutritional deficiencies, non-alcoholic fatty liver disease [NAFLD], polycystic ovary syndrome [PCOS], quality of life, health services use and costs, short-term psychiatric problems), especially when based on a sample size of at least 80 % with follow-up of 2 years and beyond. In a review of bariatric literature by Puzziferri et al., to identify studies that had 80 % or greater follow-up at 2 years and beyond, < 3 % of studies (29/1136) met this inclusion criterion. Not all studies reported adequate weight loss data or outcome data on diabetes, hypertension, and dyslipidemia [61]. The authors state that the estimates of the treatment effect are very likely biased (overestimated) due to missing weight loss and other outcome data on representative samples. It is suggested that bariatric studies use more rigorous methods of patient engagement and retention in order to mitigate loss to follow-up [61].

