#### Sample size calculation

The primary outcome for the sample size determination was defined as successful weight loss at 12 months after bariatric surgery. This was calculated as percentage of patients who attain (>50 % EWL) at 12 months post-surgery. Sample size was estimated using an online calculator for population surveys as follows: *n* = (Z^2^ × P (1 – P))/E^2^ where Z = value from standard normal distribution corresponding to desired confidence level (Z = 1.28 for 80 % CI), P is expected true proportion and E is desired precision (half desired CI width). Assuming that 50–60 % of patients undergoing LSG will achieve the primary outcome of weight loss (>50 % EWL), a total of 165 patients will be required for a precision of ±5 % at a confidence level of 80 %. To account for missing information from some patients, the sample size has been inflated to 200.

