
### Data analysis

Non-identifying patient information obtained from the standardized case report forms used to collect patient information at baseline, administrative records and medical chart reviews were entered into a Statistical Package for Social Sciences database. All statistical analyses will be performed using IBM SPSS Statistics for Windows, version 20.0 [75]. Descriptive analysis will include demographic details of patients pre-surgery and clinical information collected at the time of surgery. In each analysis to be conducted to address the six main research objectives for this program, categorical variables (such as 30-day complication rate and mortality; and long-term complications e.g., gastro esophageal reflux, micronutrient deficiencies) will be presented as frequencies and chi-square tests conducted to identify differences in pre–post surgical outcomes. Continuous variables with a normal distribution will be reported as means ± SD. Variables with a non-normal distribution will be reported as medians and interquartile ranges. For example, health services use such as number of physician visits often has a non‐normal distribution; therefore median and quartiles will be reported when comparing use pre‐ and post‐surgery. The Analysis of Variance (ANOVA) or the paired t-method will be used to assess differences in continuous outcome pre and post-surgery. Pairwise-comparison of pre with post-surgical patients’ outcomes at 3, 6, 12, 18 and 24 months will be done using matched t-tests for continuous outcomes such as BMI. Regression analyses methods will be performed to identify independent predictors of outcomes of interest (i.e., reduction in weight and/or BMI, including predictors of successful weight loss; improvement or resolution of co‐morbid conditions (i.e., diabetes, hypertension, dyslipidemia, NAFLD, PCOS); changes in prescription and over-the-counter medication use; improvement in measures of health‐related quality of life. For continues outcomes, mean differences, standard errors, 95 % confidence intervals and p-values will be presented. For categorical outcomes, odds ratios and 95 % confidence intervals will be presented. Generalized estimating equations with binary logistic regression will be used for all response or outcome events to take into account the correlations between repeated measures post-surgery providing an estimated adjusted odds ratio and 95 % confidence intervals. Statistical significance is set at *p* < 0.05.

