To examine the predictors of change in patient’s 2 years post-surgery, MIXED modelling regression approach [76, 77] implemented in SPSS will be used to assess baseline patient’s factors that determine individual changes in individual maintaining weight loss over the 24 months. The mixed modeling approach will also allow us to take into account the correlations between repeated measures and accounts for missing data over time. Statistical significance effect of factors producing changes or reduction in weight and/or BMI, including predictors of successful weight loss overtime in the 24 month post-surgery would be set at *p* < 0.05. Cost-effectiveness will be performed to evaluate the economic consequences associated with LSG. The economic analyses will be carried out on a per protocol basis and would be based on patients for whom there was complete resource use and health outcome data provided by the NL Centre for Health Information.

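### Weight and BMI change at each visit is tied to matched t-tests on patients with both measurements, while the mixed model credited with handling missing data is kept for predictors

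*Protocol article*

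**What the plan says.** **Pre/post change.** Under Data analysis, the comparisons of pre-surgical with post-surgical values "at 3, 6, 12, 18 and 24 months will be done using matched t-tests for continuous outcomes such as BMI". The sentence before it offers ANOVA or the paired t-method for continuous outcomes in general.

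**Mixed model.** Later in the same section a mixed model in SPSS is planned to find the baseline factors that determine individual change over 24 months. It is described as a way to "take into account the correlations between repeated measures and accounts for missing data over time".

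**Missing weights in the rationale.** Under Knowledge gaps the protocol reports the conclusion of a review of the bariatric literature, that "estimates of the treatment effect are very likely biased (overestimated) due to missing weight loss" and other outcome data. The Discussion returns to the subject: few bariatric studies have enough follow-up (above 80 %) to limit bias, and the open question is whether weight loss lasts.

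**The 12-month proportion.** "The primary outcome for the sample size determination was defined as successful weight loss at 12 months after bariatric surgery", meaning the percentage of patients above 50 % EWL. On missing data the same section says: "To account for missing information from some patients, the sample size has been inflated to 200".

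**The concern.** A matched t-test at a given visit needs a baseline value and a value at that visit. A patient who misses the visit drops out of that comparison, so the five comparisons can rest on five different groups. The pattern of means from 3 to 24 months then mixes real change within patients with change in who was measured. Conventional repeated-measures ANOVA does not solve this, because it drops every patient with an incomplete record.

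The protocol gives selective missing weights as a reason why earlier results are probably too favourable, and it already plans a method that uses every available weight. It does not apply that method to the mean weight changes. At stake is the size of the reported weight loss and the ability to see regain. Statistical significance is hardly at risk, since a BMI loss of the size seen after this surgery would be significant under either method.

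The proportion above 50 % EWL raises a related, weaker point. Enrolling 200 instead of 165 keeps the interval narrow, but it does not move the estimate back towards the whole cohort if the patients not seen differ from those seen.

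**Working it through.** **1. The plan's own sample size.** Inputs from Sample size calculation: "Z = 1.28 for 80 % CI", an expected proportion of 50–60 %, E = 0.05, and "a total of 165 patients will be required for a precision of ±5 % at a confidence level of 80" %. The formula is n = Z² × P(1 − P) / E².

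- P = 0.50, Z = 1.2816: 1.2816² × 0.25 / 0.0025 = 164.24, rounded up to 165. The stated figure is reproduced.
- P = 0.50, Z = 1.28: 163.84, rounded up to 164.
- P = 0.60: 158. So 165 is the conservative end of the range.

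**2. Missing share implied by the inflation.** 1 − 165/200 = 17.5 %. The protocol states no rate, so this figure is inferred.

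**3. What the inflation protects.** With 165 patients seen and 55 % successful, the 80 % half-width is 1.2816 × √(0.55 × 0.45 / 165) = 0.0496, or about 5.0 points. Precision is kept.

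**4. What it does not protect.** If a share d is missing and success among the missing is lower by a gap g, the proportion among patients seen exceeds the whole-cohort proportion by d × g. The gaps below are assumptions. The last column is the coverage of the nominal 80 % interval when the whole-cohort rate is 55 %.

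| Assumed gap (points) | Bias at 17.5 % missing (points) | Coverage of 80 % CI |
|---|---|---|
| 10 | 0.175 × 10 = 1.75 | about 76 % |
| 20 | 0.175 × 20 = 3.5 | about 63 % |
| 30 | 0.175 × 30 = 5.25 | about 46 % |

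The bias passes the planned 5 points only when the gap exceeds 5 / 0.175 = 28.6 points.

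At the extremes, with 55 % success among those seen, the whole-cohort figure is 0.825 × 55 = 45.4 % if no missing patient succeeded, and 45.4 + 17.5 = 62.9 % if all did. With 60 % among those seen, the limits are 49.5 % and 67.0 %.

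**5. Mean BMI change.** An illustrative simulation used 2,000 cohorts of 200 patients. Baseline mean BMI was 49, the average given in the Discussion. The rest was assumed: mean BMI of 35 at 12 and 24 months, strongly correlated visits, and permanent dropout that was likelier in patients who had lost less by the visit before.

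| Visit | Seen | True mean loss | Paired, attenders only | Likelihood-type estimate |
|---|---|---|---|---|
| 12 months | 87 % | 14.0 | 14.34 | 13.99 |
| 24 months | 76 % | 14.0 | 14.79 | 13.98 |

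The paired analysis overstates the loss by 0.34 / 14.0 = 2.4 % and 0.79 / 14.0 = 5.6 %. The likelihood-type estimate, standing in for the mixed model, removes the excess because dropout here depends only on weights already observed.

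**The case against.** The other side has several good arguments, and some of them narrow the point.

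- **A condensed article.** A rule for patients without a 12-month weight may well stand in a fuller protocol or analysis plan. This is correct, and the lack of such a rule is not treated here as an error. It does not help the matched t-tests, which the article itself fixes.
- **Inflation is not the only provision.** A reader might infer that it is. But %EWL is defined from the weight at the last follow-up, which on one reading lets an earlier weight stand in. The protocol also describes Tele-health visits and other measures against attrition. Those measures reduce missing data; they do not analyse what is still missing.
- **Regain and dropout.** It is tempting to say that patients who regain weight stop attending, so the results will be inflated. The document gives no such mechanism. It reports overestimation in other studies, and it cites maximum weight loss after LSG at 24 and 36 months, which makes regain a weak explanation for weights missing at 12 months.
- **Expected retention.** 165 of 200 is 82.5 %, above the 80 % that the protocol treats as adequate. This limits the likely harm but does not show that the remaining patients are a random subset.
- **GEE.** A reader might conclude that the planned logistic GEE models are valid only if data are missing completely at random. That is too absolute, because a model with covariates also tolerates missingness that depends only on those covariates. GEE is planned for correlation, however, and yields odds ratios, not the 12-month proportion.
- **Visits after 24 months.** The stated objective runs to 2–4 years while the tests and model stop at 24 months. This is a matter of scope: follow-up was due to end in September 2016, so later visits may exist only for patients enrolled early.

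**Conclusion.** The point holds as a cheap and worthwhile improvement. The protocol commits its visit-by-visit weight and BMI comparisons to a method that uses only patients with both values. It restricts the method it credits with handling missing data to predictor questions. Given its own account of why bariatric results are overestimated, the second method should carry the main estimates.

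That the analysed group changes between visits follows from how a paired test works; the document does not name the analysis set. The size of the bias cannot be derived from the document. Under the assumed gaps it is 1.8 to 5.3 points for the 12-month proportion, and in the simulation 2.4 % to 5.6 % of the mean BMI loss. A reader might infer that the bias will exceed the planned ±5 points, but that needs a gap above 28.6 points, for which the document gives no support. The conclusion that weight falls after surgery is not in doubt.

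**What to change.** 1. Make the mixed model the main analysis of weight and BMI change. Put baseline and all post-surgical values in the response, with visit as a categorical factor. Report mean change from baseline with a 95 % CI at each visit, including annual visits after 24 months where data exist.
2. Keep the matched t-tests as a sensitivity analysis.
3. As a supporting step, report the 12-month proportion above 50 % EWL with a sensitivity analysis for missing 12-month weights. Examples are multiple imputation from the other visits, and counting missing as not successful.

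The cost is a little more analysis work on weights already being collected, in software already planned for the mixed model. The mixed model and multiple imputation rest on data being missing at random given the observed weights, which should be stated. The weight-loss estimates may come out slightly less favourable.

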**Methods:**

A population-based prospective cohort study with pre and post surgical assessments at 1, 3, 6, 12, 18, 24 months and annually thereafter of patients undergoing LSG. This study will report on short - to mid-term (2–4 years) outcomes. Patients (*n* = 200) followed by the Provincial Bariatric Surgery Program between 19 and 70 years of age, with a BMI between 35.0 and 39.9 kg/m^2^ and an obesity-related comorbidity or with a BMI ≥ 40 kg/m^2^ are enrolled. The study is assessing the following outcomes: 1) complications of surgery including impact on nutritional status 2) weight loss/regain 3) improvement/resolution of comorbid conditions and a reduction in prescribed medications 4) patient reported outcomes using validated quality of life tools, and 5) impact of surgery on health services use and costs. We hypothesize a low complication rate, a marked reduction in weight, improvement/resolution of comorbid conditions, a reduction in related medications, improvement in quality of life, and a decrease in direct healthcare use and costs and indirect costs compared to pre-surgery.

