#### Laparoscopic sleeve gastrectomy as a treatment for severe obesity

LSG began as the first stage of a two-tiered operation of duodenal switch or RYGB for very large (e.g., BMI ≥ 50 kg/m^2^) or high-risk patients [3, 22, 49, 50]. Sleeve gastrectomy involves the surgical resection of the greater curvature and fundus of the stomach which creates an elongated tube or stomach ‘sleeve’ along the lesser curvature. This sleeve has a volume of 60–100 ml, effectively restricting caloric intake and increasing feelings of satiety. Removal of the fundus has also been associated with endocrine and metabolic effects [21], for example, the reduction of circulating levels of ghrelin – a hunger hormone, which may reduce the desire for food. It is not yet fully understood how LSG creates favorable metabolic changes and weight loss but this topic is a major focus of research. Since the early 2000’s, LSG grew in popularity as a stand-alone bariatric surgery because of the perceived technical ease of performing the surgery, associated obesity-related comorbidity improvement or resolution, and good short-term weight loss outcomes [25, 26]. It is now recognized as a primary bariatric surgery option and as a first-stage procedure in high-risk patients as part of a planned staged approach [26]. In a recent systematic review conducted by Victorzon in 2012, the author noted that the quantity, quality, and consistency of evidence for LSG for the treatment of obesity were low. Victorzon suggested that although numerous short-term studies had shown that LSG had good outcomes of between 45–60 % EWL, no longer term studies with >100 patients have been published [50]. For LSG, average clinically expected %EWL has been reported to be 56.1 % within the first year after surgery but there is limited data on sustained or continued weight loss longer term [51]. In a systematic review [51] the maximum weight loss reportedly occurred at 24 and 36 months following LSG surgery with %EWL’s of 64.3 % (46.1–75.0 %) and 66.0 % (60.0–77.5 %), respectively [51]. In a small study examining average %EWL 5 years following surgery %EWL was 86 % (50–103 %), but only 49 patients had complete follow-up data [52].

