#### The Newfoundland and Labrador Bariatric Surgery Cohort (BaSCo) study

##### Study objective

The objective of the current study is to examine short- to mid-term outcomes (2–4 years) associated with LSG. Eligible patients who have undergone LSG will be followed during and after surgery to assess health and other outcomes. Specific study objectives are to examine:30-day complication rate and mortality, and long-term complications (e.g., gastroesophageal reflux, micronutrient deficiencies).reduction in weight and/or body mass index (BMI), including predictors of successful weight loss.improvement or resolution of co‐morbid conditions (i.e. diabetes, hypertension, dyslipidemia, NAFLD, PCOS).changes in prescription and over-the-counter medication use.improvement in measures of health‐related quality of life andthe economic consequences associated with LSG (e.g., direct costs and indirect costs).

In the short- to mid-term we hypothesize a low rate of complications, a marked reduction in weight, improvement/resolution of comorbid conditions, a reduction in obesity-related medications, an improvement in quality of life, and a decrease in direct healthcare and indirect costs compared to pre-surgery costs.

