## Discussion

In summary, the demand for LSG as a stand-alone procedure is growing in popularity as a treatment for class II and III obesity. In a joint report “Developing a Research Agenda to Support Bariatric Care” published by the CIHR and the Canadian Obesity Network in 2010, the gaps in research related to bariatric surgery were highlighted [78]. Although LSG was not specifically highlighted in the report, compared to other bariatric surgeries, research on LSG as a treatment for severe obesity is limited due to its relatively recent provision as a stand-alone procedure. The start-up of a bariatric surgery program offering LSG as a treatment for severe obesity combined with the limited research on LSG provided an opportunity for research. Consequently, an Integrated Knowledge Translation Team was established at Memorial University, comprised of academic researchers, healthcare professionals, decision-makers, and policy makers, and a program of research on bariatric care was developed to address key gaps in the research literature. One of the studies designed and implemented within this program of research and presented in this paper is a quasi-experimental study that aims to address current knowledge gaps in LSG by generating prospective, population-based Canadian outcome data. This study is being conducted in a provincial bariatric surgery program within a tertiary care teaching centre and the results will be generalizable to similar programs offering bariatric surgery. A current review continues to highlight a major concern previously identified by others [79, 80] associated with bariatric surgery as a treatment for obesity. It is not the magnitude of initial weight loss which has been well documented but the mid- to long-term sustainability of weight loss that is under question. Very few bariatric studies report long-term results with sufficient patient follow-up (>80 %) in order to minimize biased results. In addition, insufficient evidence exists regarding long-term outcomes for LSG [61]. In response to this concern and as part of the current study protocol, a clinical database to house all program data in order to monitor longer-term (>5 years) patient health outcomes has been developed which will also allow for data linkages with administrative data to examine health care use and costs in the future. Further interventions being used in order to decrease attrition and increase patient engagement include the use of technology (e.g., Tele-health and webinar sessions for educational purposes). As of August 2015, 100 % recruitment has been achieved with completion of follow-up to be completed by September 2016 with study results to be published in late 2016 and early 2017. Our study population is 82 % female, with an average age, weight, and BMI of 44 years, 135 kgs and 49 kg/m^2^, respectively. The prevalence rates of hypertension and dyslipidemia were approximately 50 and 43 % had T2DM. Our study participants are similar to other patient populations that are eligible for and undergoing bariatric surgery elsewhere in Canada [15, 21], increasing the external validity of our study findings.

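### The objective covers 2–4-year outcomes and the abstract lists regain, but no weight analysis with a stated time goes past 24 months and none measures regain

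*Protocol article*

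**What the plan says.** **The question.** Under Study objective: "The objective of the current study is to examine short- to mid-term outcomes (2–4 years) associated with LSG". The abstract repeats the 2–4-year horizon and gives as its second outcome "2) weight loss/regain". The Knowledge gaps section includes durability of weight loss among the outcomes with limited data. The Discussion says that initial loss is well documented and that it is "the mid- to long-term sustainability of weight loss that is under question".

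**The success criterion.** Under Sample size calculation: "The primary outcome for the sample size determination was defined as successful weight loss at 12 months after bariatric surgery". The section on the primary outcome also dates the >50 % EWL proportion at 12 months.

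**The analyses.** The Data analysis section compares pre- and post-surgical "outcomes at 3, 6, 12, 18 and 24 months will be done using matched t-tests", and plans a mixed model for predictors of "individual changes in individual maintaining weight loss over the 24 months".

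**The measures.** The primary-outcome section defines weight change from baseline. %EWL and %TWL run from the weight at surgery to the weight at last follow-up.

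**The data.** Table 1 schedules weight up to 24 months and once a year after that.

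**The concern.** The study asks about years 2 to 4 and names regain as an outcome. Its dated criterion falls at 12 months, and its dated analyses end where the 2–4-year window opens. Results to 24 months describe how much weight is lost up to about the point of maximum loss. They say little about what happens afterwards, which the Discussion presents as the open question. If nothing changes, the report could meet its stated analyses in full and still contain no estimate for year 3 or 4 and none of regain, although the weights to produce both are scheduled.

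**Working it through.** **1. The plan's own figure.** With n = Z²P(1 − P)/E², P = 0.50 and E = 0.05:
- Z = 1.28 gives 1.6384 × 0.25/0.0025 = 163.84, so 164.
- Z = 1.2816 gives 164.24, so 165.

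The stated 165 reproduces. It supports the 12-month proportion only. The point below does not depend on it, and no corrected sample size follows.

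**2. Each weight analysis against the objective.**

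| Element | Stated time | Reaches past 24 months? | Measures regain? |
|---|---|---|---|
| >50 % EWL proportion | 12 months | No | No |
| Matched t-tests | 3 to 24 months | No | No, each is against pre-surgery |
| Mixed model | 24 months | No | No measure defined |
| %EWL, %TWL | Last follow-up | Yes, where later weights exist | No, change from surgery |
| ≥5 and 10 % loss | None | Not stated | No |
| Predictor regressions, GEE | None | Not stated | No regain event named |

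No row has both a stated time and reach beyond 24 months, and no row starts from an earlier post-surgical weight.

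**3. Where 24 months sits on the loss curve.** The section on LSG as a treatment for severe obesity cites mean EWL of 56.1 % within the first year, 64.3 % at 24 months (range 46.1–75.0) and 66.0 % at 36 months (range 60.0–77.5).
- First year to 24 months: 64.3 − 56.1 = 8.2 points.
- 24 to 36 months: 66.0 − 64.3 = 1.7 points, with overlapping ranges.

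So 12 months precedes the maximum, and 24 months is at or near it.

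**4. What last follow-up would mix.** The Discussion has recruitment complete as of August 2015 and follow-up ending September 2016. Surgery dates are not given, so two assumed patterns bracket the answer. Both start in May 2011, when the clinic opened, which is 64 months before September 2016, and both assume every visit is attended.

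*Slow: uniform over the 51 months to August 2015.* The last patient has about 13 months. The share reaching visit f is (64 − f)/51:
- 24 months: 40/51 = 78 %
- 36 months: 28/51 = 55 %
- 48 months: 16/51 = 31 %

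The last available visit would then be before 24 months for about 22 % of patients, at 24 months for 24 %, at 36 months for 24 % and at 48 months or later for 31 % (rounded).

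*Fast: 100 a year, so 200 by May 2013.* Everyone has at least 40 months and reaches the 36-month visit. The share reaching 48 months is 16/24 = 67 %.

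Under slow accrual, one last-follow-up average pools patients from about 1 to more than 4 years and estimates no single time point.

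**5. Precision at later visits.** The half-width for a proportion of 0.50 at 95 % confidence is 1.96 × √(0.25/n):
- n = 200: 6.9 points
- n = 110 (55 % of 200): 9.3 points
- n = 63 (31 % of 200): 12.3 points

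Estimates at 36 and 48 months remain usable but are wider.

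**The case against.** The best reply has four parts.

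- **Later weights are not ignored.** Last-follow-up %EWL and %TWL can include them, and the regressions and GEE have no stated cut-off. This stands, so it would be wrong to say that no stated analysis can use the 36- and 48-month weights. But a last-follow-up value has no fixed time, and the undated models name neither a late time point nor a regain event.
- **Twelve months is not the only view of success.** The mixed model also covers predictors of successful loss over 24 months, and the ≥5 and 10 % proportions carry no date. This stands too. It still leaves years 2 to 4 without a dated analysis.
- **Detail may sit in the full protocol or analysis plan.** The lack of a formal regain definition alone would not be a finding in an article. Here, though, the article does not leave the times open: it fixes them at 12 and 24 months against a stated horizon of 2–4 years.
- **Sustainability is not a listed objective.** Correct: it appears under Knowledge gaps and in the Discussion, where part of the response is a database for monitoring beyond 5 years. The mismatch rests on the 2–4-year horizon and the listed regain outcome, which are the study's own terms.

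A reader might go further and infer that the analysis stops before loss peaks. The article does not support that: it says "the maximum weight loss reportedly occurred at 24 and 36 months following LSG surgery", and those means differ by 1.7 points. They are review averages, so they do not show that individual patients are still losing at 24 months.

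A reader might also put the 12-month and 24-month success proportions 12 to 17 points apart. That rests on an assumed normal spread (SD 15–25), which the documents do not give, and on treating a mean from within the first year as a 12-month mean. The 12-month proportions it implies, 60–66 %, lie at or above the plan's own 50–60 %. The point does not rely on it.

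**Conclusion.** The mismatch is real but bounded. The stated horizon is 2–4 years and regain is a listed outcome, yet every dated weight analysis ends by 24 months, the lower edge of that horizon and at or near the cited maximum loss. Nothing is measured from an earlier post-surgical weight.

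It does not follow that regain and durability cannot be answered. Yearly weights are scheduled, and regain between 12 and 24 months can be derived from the repeated measures. The gap lies in the stated analyses, not in data collection.

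This conclusion comes from comparing the article's own sections and needs no assumption. Only the shares reaching each visit (78 %, 55 % and 31 % under slow accrual; all at 36 months and 67 % at 48 months under fast accrual) and the resulting precision rest on assumed surgery dates and full attendance.

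**What to change.** - Keep the 12-month >50 % EWL proportion for the sample-size statement. A new key outcome at 24 months is not needed, and naming one after recruitment closed would have its own pre-specification cost.
- Extend the planned mixed model to all scheduled weights, including 36 and 48 months where reached.
- Report %EWL and %TWL at fixed visits, not only at last follow-up.
- Add a regain measure: change from the 12-month weight, and loss of >50 % EWL status, at 24 months and later.
- If this is not done, limit the weight objective and the conclusions to 24 months.

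**Cost.** Only the analysis wording changes, because the weights are already scheduled. The 36- and 48-month estimates will be less precise. They will also come from patients operated on earlier in the programme, who may differ from later ones, so report the number and the calendar period of surgery contributing at each visit.
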